### Monitoring

An independent data and safety monitoring board (DSMB) will be established prior to the start of the trial. All the serious adverse events (SAE’s) (intra uterine fetal death (IUFD), uterine rupture, severe maternal and neonatal morbidity such as IC/NICU admission and related events such as placental abruption directly after insertion of Foley catheter) will be reported within 48 hours to the CCMO (central commission human related research). All SAEs will be reported to the DSMB at 300 and 600 inclusions when the interim analysis will take place, or when in total 5 SAEs are reported, whichever comes first. Prior to the start of the trial the DSMB defined criteria to terminate the trial prematurely. The DSMB will perform 2 interim analyses: after recruitment of 300 and 600 patients. These interim analyses will be conducted independently of the research group, and will take into account safety (infection, asphyxia, haemorrhage) as well as efficacy. The study will be terminated prematurely for efficacy according to the Haybittle rule when there is a difference with P <0.001.

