### Sample size

To calculate an adequate sample size we searched the literature for comparisons between oral misoprostol and Foley catheter. There is only one study which directly compared induction of labour with oral misoprostol and Foley catheter. This study does not report on our primary outcome measures which makes it insufficient to use for our power calculation [10]. A few studies reported on a comparison of vaginal misoprostol and prostaglandin E2, but different dosages were used and from the reported outcome parameters it was not possible to calculate the composite outcome we use [6]. Therefore we used data from the PROBAAT trial, comparing prostaglandin E2 (prostin) with Foley catheter [9]. In the Probaat trial the incidence of the composite outcome of pH ≤ 7.05 and/or an Apgar < 7 at 5 minutes (at least one known) and/or haemorrhage ≥1000 cc post partum was 12.7% when a Foley catheter was used and 16.4% when Prostaglandin E2 gel was used. We expect the incidence of the composite outcome to be lower when using oral misoprostol than when using prostaglandin E2 but slightly higher than when a Foley catheter is used [5]. We expect that about 25% of umbilical cord pH’s will be missing, while the 5 minute Apgar will be complete in nearly all cases. So, if the umbilical artery pH data will be missing, neonatal outcome will be classified as abnormal if the 5 minute Apgar will be <7 and as normal if the Apgar was ≥ 7. With a power of 80% (1-β) and a one-sided 0.05 risk of type I error (α), we need 1860 participants (930 per group) to demonstrate non-inferiority, i.e. that the absolute difference in the composite outcome will be less than 5% in the misoprostol group compared to the Foley catheter group, when assuming that the composite outcome was 12.7% in the Foley catheter group and 13.7% in the misoprostol group and an 5% exclusion rate from the per protocol analysis. This sample size will also give us more than 80% power to demonstrate non-inferiority, i.e. less than 5% increase in the proportion of caesarean sections when using misoprostol compared to Foley catheter, assuming 23% caesarean sections in both groups [9]. We used NQuery Advisor 7.0, with the two group test of equivalence in proportion (NQueryAdvisor; Machin 1987) to calculate the sample size.

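### A single fetal death or uterine rupture goes to the CCMO within 48 hours but is scheduled to reach the DSMB only in a batch, an avoidable delay of tens of women, and at worst about 300

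*Protocol article*

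**What the plan says.** All of this stands in the Monitoring section of the protocol article.

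- **Which events count.** The list of SAEs opens "All the serious adverse events (SAE’s) (intra uterine fetal death (IUFD), uterine rupture, severe maternal and neonatal morbidity such as IC/NICU admission". Fetal death, rupture and admission to intensive care therefore belong to one class.
- **Route to the CCMO.** These events "will be reported within 48 hours to the CCMO".
- **Route to the DSMB.** The scheduled reports come first: "All SAEs will be reported to the DSMB at 300 and 600 inclusions when the interim analysis will take place". An event count can bring a report forward; the sentence ends "or when in total 5 SAEs are reported, whichever comes first".
- **What the board does.** "The DSMB will perform 2 interim analyses: after recruitment of 300 and 600 patients". The analyses are run independently of the research group and "will take into account safety (infection, asphyxia, haemorrhage) as well as efficacy". The board also defined, before the trial began, the criteria for ending it early.

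The Abstract says only that serious events will be monitored and reported to an independent board, and gives no time limit. No other section gives the board a route for a single event.

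**The concern.** One set of events runs on two clocks, and the slower clock belongs to the board with the monitoring task. The article gives the interim analyses and the termination criteria to the DSMB. It gives the CCMO neither, and nothing requires the CCMO to pass a report on. The article does not say in words that the board looks at harm by arm, but that is a reasonable inference from its running the interim analyses on safety and efficacy.

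The early trigger does not separate events by gravity. Five neonatal intensive-care admissions fire it, while one fetal death or one rupture does not. From one to four catastrophic events, even all in one arm, could wait for the next look while randomisation goes on.

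The trigger is also ambiguous. A total of five may mean the first five SAEs of the trial, after which the trigger has no further effect, or every further five.

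At stake is the timeliness of safety oversight. The primary analysis is not affected.

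**Working it through.** The article gives no reporting delay and no SAE rate, so there is no figure of its own to reproduce. The size follows from the stated triggers plus an assumed rate.

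**Inputs from Monitoring:** scheduled reports at 300 and 600 inclusions; event trigger at 5 SAEs in total; CCMO deadline 48 hours.

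**Assumption (not in the article):** SAEs occur independently, with probability p per woman, and p lies between 0.5% and 4%.

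**Step 1, longest wait up to woman 600.** An event at woman 1 that is reported at woman 300 waits 300 − 1 = 299 women. An event at woman 301 that is reported at woman 600 waits 600 − 301 = 299. The first case needs fewer than five SAEs among the first 300 women. The second needs the five-event trigger not to fire between women 301 and 600.

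**Step 2, how often the trigger fires before woman 300.** P(at least 5 in 300) = 1 − Σ C(300,k) p^k (1−p)^(300−k), summed over k = 0 to 4. Results are in the table.

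**Step 3, wait of a catastrophic event at a random position x in the first 300 women.** The wait is W = T − x, where T is the first report at or after x. The event itself counts towards the five.

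- Cumulative count: T is the position of the fifth SAE if x is not beyond it, otherwise 300.
- Restarting count: T is the next of the 5th, 10th, 15th … SAE, or 300 if none follows.

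Each rate was simulated 20,000 times.

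| Assumed SAE rate | P(at least 5 in 300) | Mean wait, cumulative | 90th percentile | Mean wait, restarting | 90th percentile |
|---|---|---|---|---|---|
| 0.5% | 1.8% | 145 | 267 | little changed | little changed |
| 1% | 18.4% | 127 | 257 | little changed | little changed |
| 2% | 71.8% | 87 | 195 | little changed | little changed |
| 3% | 94.8% | 74 | 160 | about 60 | about 139 |
| 4% | 99.3% | 77 | 167 | about 46 | about 107 |

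A separate simulation of the cumulative reading gave means of 147, 128, 87, 74 and 77, which agree within simulation error. As a sanity check, if the trigger never fired, the mean wait would be (0 + 1 + … + 299)/300 = 149.5 women, close to the 0.5% row. On the cumulative reading the mean stops falling between 3% and 4%: the trigger fires sooner, so more events come after it and wait for woman 300.

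**Step 4, a measure that does not depend on the reading.** The first SAE of the trial waits for the fifth or for woman 300 whether or not the count restarts. Given that at least one SAE occurs in the first 300 women, its mean wait is about 185, 202, 175 and 131 women at 0.5, 1, 2 and 3%. It is about 80 at 5% and 40 at 10%.

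**Step 5, after the change.** A report on the CCMO clock reaches the board within 48 hours at any point in enrolment.

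**The case against.** The case on the other side has five parts.

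- **Two recipients at two frequencies are not a contradiction.** That is correct, and none is claimed. The point is that a rule stated in full is a weak one.
- **A DSMB charter or the full protocol may provide for immediate notice, and the termination criteria are not shown.** That is possible. But the article does not leave the timing to another document. It states when SAEs go to the board, so if a faster route exists this sentence should say so.
- **The event is not unseen.** The CCMO hears within 48 hours and the trial is open-label, so caregivers know the treatment given. This stands as a mitigation. It does not put the event before the board that holds the interim analyses and the termination criteria.
- **The assumed rates may be too low.** Intensive-care admissions count as SAEs, so rates above 4% are plausible. This stands. If the count restarts, mean waits fall to about 36 women at 5% and 19 at 10%. Accrual is not given, so no wait converts to calendar time.
- **One or two rare events say little about a difference between arms.** This is true as statistics, and it limits the weight of the point. Whether one event matters is for the board to judge, and it can do so only once told.

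A reader might infer three stronger things that the article does not support. First, that the board cannot act on a single event: the text sets reporting times and does not bar earlier contact or a request from the board. Second, that the trigger is certainly used up after five SAEs: the text does not say whether the count restarts. Third, that a wait of about 300 women is typical: it is the extreme, and in the first window it needs fewer than five SAEs by woman 300.

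**Conclusion.** The point holds as an avoidable delay in safety reporting. Followed as written, Monitoring lets a single death or uterine rupture go unreported to the DSMB until the next trigger, although a 48-hour report of the same event already exists.

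Up to woman 600 the worst case is about 300 women. In the first 300 women the mean wait is about 74 to 145 women on the cumulative reading. At rates of 3 to 4% it is about 46 to 60 if the count restarts; at 0.5 to 2% the two readings hardly differ. These figures rest on an assumed SAE rate of 0.5 to 4% per woman and on independent events. The existence of a delay does not depend on the rate, but its length does. The period after woman 600, for which no scheduled report is named, is not part of this sizing.

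This is a cheap improvement to oversight. It does not call the primary analysis into question.

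**What to change.** Amend the Monitoring section in two places.

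1. State that each intrauterine fetal death, maternal or neonatal death and uterine rupture is sent to the DSMB, with the allocated arm, in the same 48-hour report that goes to the CCMO. Because the trial is open-label, giving the arm breaks no blind.
2. Keep the batch report and the count of five for all other SAEs, and state whether that count restarts after each report.

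The DSMB charter should carry the same wording; if it already provides for immediate notice, Monitoring should be brought into line with it. The change concerns reporting only and sets no stopping rule. It costs a sentence or two in the protocol and charter, a second recipient for an existing report, and a few unscheduled contacts with the board.

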### Ethical considerations

This study has been approved by the National Central Committee on Research involving Human Subjects (CCMO - NL 35278.018.11.), by the ethics committee of the Academical Medical Centre (Ref. No. 2011_010#B2012219). The boards of directors of all participating hospitals approved local execution of the study.

## Discussion

In Western countries, labour is induced in 20-30% of all pregnant women for various reasons. Until now different methods for labour induction are used. In literature contradictory results are reported regarding efficacy and safety of the induction methods. The outcome of our recent study which compared prostaglandin gel to a Foley catheter was that the Foley catheter showed fewer maternal and neonatal side-effects and was as effective as prostaglandin gel [9]. Another widely used method of labour induction is the administration of misoprostol. Misoprostol is recommended by several (inter)national guidelines, based on cost-effectiveness [6,8]. However, randomised controlled trials are underpowered to investigate the estimators of interest. Therefore we will compare in an adequately powered randomised open-label controlled trial induction of labour at term with a Foley catheter to oral misoprostol. Taking into account the possible risks, costs and women’s preferences; this study could assess the safest, most cost-effective and patient friendliest way of inducing labour with an unfavorable cervix. Eventually this study could contribute to achieve consensus in the guidelines, thereby improving the care for over 20% of all the pregnant women in western countries from who labour will be induced.

## Abbreviations

CCMO: Central Committee on Research Involving Human Subjects; in Dutch: Centrale Commissie Mensgebonden Onderzoek; DSMB: Data safety monitoring board; FHR: Fetal heart rate; (S)EA: (Serious) Adverse event.
